#### Power Analysis

Given that the goal of this study is to describe patterns and associations and not evaluate a particular intervention, there is no formally defined primary end point. Hence, our power analysis focuses on describing the effect sizes that can plausibly be detected with the given analytic sample size of 200 families (accounting for approximately 20% attrition from our baseline sample).

Key outcomes are the mean levels of the 4 food parenting practice domains. With our sample size, 95% CIs for these means based on the total sample will have a margin of error of +0.17 or –0.17 SDs, corresponding to a small effect size per usual guidance [62]. For the clustering analyses, most participants will have at least 32 longitudinal observations spanning 8 days of data collection. Hence, we anticipate having an adequate sample size to accurately calculate individual summaries of the mean use, consistency, and endurance of food parenting practices, which will be used in the k-means clustering algorithm. To ensure that we can adequately characterize clusters based on demographic characteristics, we plan to restrict our clustering approaches so that they identify no more than 5 clusters, yielding an average cluster size of at least 30 participants; we will also restrict the minimum cluster size to 15 participants.

We calculate the detectable effect size of an analysis comparing mean child HEI between 2 groups of size n=100, for example, comparing families above and below the median of food parenting consistency or endurance. We have 80% power to detect a difference of 0.4 SDs, corresponding to the difference of approximately 4.7 units in total HEI given an HEI SD of 11.6 units in children aged 2 to 4 years enrolled in the NET-Works study [63]. For comparing 2 groups of size n=50 (eg, quartiles), we will have 80% power to detect a difference of 0.57 SD, or 6.7 HEI units. Power for associations between continuous summary measures of food parenting practices and total HEI will be higher.

The study will yield at least 32 observations per person (4 event or signal responses per day ×8 days), resulting in a total of 6400 data points on each domain. We conducted a simulation to assess the power to detect an association between a binary covariate and a domain score using parameter values informed by data from Kids EAT! [15,20]. For covariates that vary only between individuals, we estimate 80% power to detect a difference of 0.55 items endorsed per signal survey for a given domain. Because the maximum number of possible items endorsed per signal survey ranges from 4 to 7 across domains, an effect of this magnitude seems plausible. For momentary predictors, we have 80% power to detect differences of 0.14 items endorsed per signal survey. In general, power calculations using binary covariates tend to be more conservative than those using continuous covariates; therefore, we anticipate the actual power to be higher than estimated in this simulation.

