## Methods

### Study Design and Participants

Preschool Plates is a longitudinal cohort study examining the impact of food parenting practices on the dietary intake of children aged 3 to 5 years. At baseline, a total of 273 parent-preschooler dyads were consented and enrolled, and 254 (93%) dyads completed baseline data collection.

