### Statistical Analysis Plan

#### Overview

R (R Foundation for Statistical Computing) will be used for data cleaning and main analyses. Distributions of key outcome variables will be assessed and transformed if necessary. Unless otherwise specified, hypothesis tests will be conducted using a 2-sided α level of .05.

EMA responses will be aggregated to derive scores for each of the 4 food parenting practice domains during each data collection period. Given the unequal number of questions related to each domain, 2 versions of domain scores will be created by computing (1) the number of items endorsed in each domain and (2) the proportion of items endorsed in each domain. Domain scores will be calculated for responses given at each event prompt (typically 2-8 per day over each 8-day data collection period).

Food parenting practice domain scores will be aggregated and compared visually and statistically at the event level (eg, breakfast, lunch, snack, and dinner) and by time period (eg, 9 AM to noon, 3 PM-5 PM, and 5 PM-9 PM). In addition, for each data collection period, we will fit linear mixed models for each domain of the form (M1) *D_ij_ = β_0_ + β_1_Z_ij_ + β_2_X_i_ + b_i_ + ε_ij_*, where *D_ij_* is the domain score for person *i* at event prompt *j*, *Z_ij_* is the event characteristic of interest (meal or time period indicator), *X_i_* is a set of baseline characteristics for person *i*, *b_i_* is a person-specific random effect, and *ε_ij_* is the residual. Longitudinal response patterns in domain scores will be visualized and qualitatively compared. We will calculate each individual’s SD, IQR, and entropy of domain scores across their longitudinal observations. How between-day fluctuations in food parenting differ across individuals will be quantified using longitudinal mixed models, similar to those described above, with the event characteristics *Z_ij_* representing between-day factors such as day of the week. The SD, IQR, and entropy of residuals from these models will also be summarized to characterize between-day fluctuations.

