To examine the longitudinal impact of within- and between-day fluctuations in food parenting practices on child dietary intake, we will fit regression models for the outcome of child HEI measured from 24-hour dietary recall at time points T2 to T4. The main predictors of interest will be the individual-level summary measures of the 4 food parenting practice domains derived above. Our primary models will include the subgroup indicators classifying parents according to food parenting practice patterns, but we will also consider models that use average domain scores as well as consistency and endurance metrics. We will fit separate linear regressions for each data collection period, as well as longitudinal models that incorporate data across the time points T2 to T4. For period-specific models, we will include cluster indicators as well as consistency *z* scores that reflect the degree of within- and between-day fluctuations in food parenting practices during that period, along with relevant adjustment covariates. For longitudinal models, we will also include endurance *z* scores that reflect whether food parenting practices are maintained across data collection periods.

To identify momentary predictors of within- and- between-day fluctuations in the use of food parenting practices across time and context, we will combine the signal and event EMA survey data to understand how momentary factors (eg, mood, stress, and time constraints) affect food parenting practices. The main statistical approach will be to fit longitudinal linear mixed models of the form: (M2) *D_ij_* = *β_0_* + *β_1_W_ij_* + *β_2_X_i_* + *b_i_* + *ε_ij_*. Here, *W_ij_* represents a *vector* of momentary predictors, which will be derived by summarizing signal surveys within fixed time windows before the event *j*. Initially, we will define 

, with the superscript in parentheses indicating the number of hours before the event covered by that variable. For instance, 

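### The ±0.17 SD margin does not follow from 200 families (it should be ±0.14 SD), and the HEI detectable differences are not stated for the cluster contrasts that the plan calls primary

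*Protocol article*

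**What the plan says.** The Power Analysis section works from a "given analytic sample size of 200 families (accounting for approximately 20% attrition from our baseline sample"). The baseline sample is given under Study Design and Participants: "254 (93%) dyads completed baseline data collection". For the means of the four food parenting domains, which the section treats as key outcomes, it states that "95% CIs for these means based on the total sample will have a margin of error of +0.17" or –0.17 SD, and it calls this a small effect size.

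For child HEI, the section gives 80% power for 0.4 SD (about 4.7 units at an SD of 11.6) when comparing "2 groups of size n=100, for example, comparing families above and below the median of food parenting consistency or endurance". It then gives 0.57 SD (6.7 units) for two groups of 50, described as quartiles. It says that there is no formally defined primary end point.

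The Statistical Analysis Plan overview sets the test level: "hypothesis tests will be conducted using a 2-sided α level of .05". On the HEI models it says: "Our primary models will include the subgroup indicators classifying parents according to food parenting practice patterns". Those subgroups are k-means clusters, three to five in number. The Power Analysis caps them at five, "yielding an average cluster size of at least 30 participants; we will also restrict the minimum cluster size to 15 participants".

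**The concern.** The margin is a one-line calculation from an n printed in the same section, and it does not come out. It is the only precision figure offered for the domain means, so a reader who checks it will wonder which sample size lies behind the section.

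The HEI figures are a different matter. They are correct for the splits they describe, but those splits are not the comparison in the models labelled primary. A reader who wants to know what a null cluster result could rule out must work out which printed figure applies. Neither printed figure reaches the small clusters that the plan permits.

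**Working it through.** **1. Margin for a domain mean**

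Inputs: n = 200 (Power Analysis); 95% confidence; result in SD units.

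Half-width = 1.96/√n.

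- n = 200: 1.96/14.142 = 0.139 (0.139 also with the t quantile)
- n = 254 (baseline): 0.123
- n = 203 (254 × 0.8, exactly 20% attrition): 0.138
- n needed for 0.17: (1.96/0.17)² = 132.9, about 133; allowing for rounding of 0.17 (0.165 to 0.175), 125 to 141

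The stated figure is not reproduced. Other routes tried at n = 200:

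- 99% interval: 0.182
- Bonferroni over four domains: 0.177
- 90% interval: 0.116
- one-sample detectable difference at 80% power: 0.198

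None gives 0.17. The variance inflation that would be needed is (0.17/0.1386)² = 1.50, and none is mentioned. If SD means the SD of a single prompt, averaging about 32 prompts per parent makes the margin smaller, not larger.

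The rest of the section does use 200: two halves of 100, quartiles of 50, and 6400 data points = 200 × 32.

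**2. HEI detectable differences**

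Inputs: power 80%, two-sided α = .05, SD 11.6 (all from the article). Formula: d = (1.960 + 0.842) × √(1/n₁ + 1/n₂), checked with the noncentral t.

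The plan's own figures first:

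- 100 v 100: 2.802 × 0.1414 = 0.396 (t: 0.398), stated as 0.4
- 50 v 50: 2.802 × 0.2 = 0.560 (t: 0.566), stated as 0.57

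Both reproduce. In units, 0.4 × 11.6 = 4.64 and 0.57 × 11.6 = 6.61, against the printed 4.7 and 6.7; these are differences of rounding size.

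The same formula applied to pairwise cluster contrasts in 200 families (normal to t):

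| Contrast | SD units | HEI units |
|---|---|---|
| 3 equal clusters, 67 v 67 | 0.48–0.49 | 5.6–5.7 |
| 4 equal clusters, 50 v 50 | 0.56–0.57 | 6.5–6.6 |
| 5 equal clusters, 40 v 40 | 0.63 | 7.3–7.4 |
| minimum v average of five, 15 v 40 | 0.85–0.86 | 9.8–10.0 |
| two clusters at the minimum, 15 v 15 | 1.02–1.06 | 11.9–12.3 |

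Equal cluster sizes are an assumption; 15 is the plan's floor. Power for a 0.4 SD difference is about 43% at 40 v 40 and 19% at 15 v 15.

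**The case against.** On the margin, the case against is about consequence. The error is conservative, no sample size or test depends on it, recruitment is closed, and a margin the article calls small at 0.17 is still small at 0.14. All of that stands. It makes the correction minor but does not make the figure right.

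On HEI, the other side is stronger, and it rules out several readings that a reader might infer:

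- *That the average cluster size is misstated.* Five clusters in 200 families average 40, and 30 would match 150. But the article gives 30 as a lower bound, and 40 satisfies it. Nor does this show mixed sample sizes: n = 150 gives a margin of 0.160, so it does not explain 0.17.
- *That 4.7 units is offered as the sensitivity of the study.* The text ties it to two groups of 100, as an example, and then prints the less favourable 6.7.
- *That no printed figure applies to clusters.* Four equal clusters in 200 are 50 each, so 6.7 is in effect the four-cluster contrast. The three-cluster value lies between the two printed figures, and the five-cluster value is only 0.6 to 0.7 units above 6.7.
- *That 12 units is the typical case.* It needs two clusters both at the floor. With residual variance pooled over all 200 families it stays near 11.9, and covariates or the longitudinal models may improve on it.

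The median split is also relevant in itself, because hypothesis 4 contrasts consistent and enduring use with inconsistent or short-lived use. And a condensed article need not tabulate every scenario. What remains is that the overview labels the cluster-indicator models primary, while the HEI figures are framed only as median and quartile splits and do not reach the small clusters that the same section allows.

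**Conclusion.** The ±0.17 SD margin is wrong as stated. For 200 families it is ±0.14 SD, which makes the printed value about 23% too wide (0.17/0.139 = 1.22 to 1.23). This rests on a simple mean over 200 independent families, with SD taken between families. Only an unstated smaller n (about 133) or an unstated variance inflation (about 1.5) would rescue the figure. The interpretation in the article is unaffected.

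The HEI part is a clarification, not an arithmetic error: both printed figures are sound for their own splits. For the models called primary, equal clusters detect about 5.6, 6.6 and 7.3 units with three, four and five clusters. Two clusters at the permitted minimum detect about 12. These values assume SD 11.6, 80% power, two-sided .05, complete HEI data on 200 families, no covariate gain and no multiplicity correction. The documents do not support a change of primary model on this ground; moving to the continuous consistency and endurance metrics would be a design trade-off.

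**What to change.** In the Power Analysis section, restate the margin as ±0.14 SD for 200 families (optionally ±0.12 SD for the 254 families at baseline). If 0.17 was intended, state the smaller n or the variance inflation that yields it.

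After the 50 v 50 figure, add one sentence: for the cluster-indicator models, pairwise contrasts between equal clusters detect about 5.6, 6.6 and 7.3 HEI units with three, four and five clusters, rising to about 12 units for two clusters of 15, before covariate adjustment or multiplicity correction. Noting that the 50 v 50 case corresponds to four equal clusters would link the printed figure to the primary models.

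The cluster-size sentence and the choice of primary model can stay as they are. The cost is a few words of text; design, data collection and analysis are unchanged.

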#### Ecological Momentary Assessment

EMAs were used to assess specific food parenting practices used during shared eating occasions, as well as to identify momentary predictors of within- and between-day variability in use of specific food parenting practices.

The EMA protocol included 2 distinct types of assessments. the first was event-contingent assessments; for these, caregivers were asked to complete an EMA survey after every eating occasion during which they were present with the enrolled child. Event-contingent assessments were initiated by caregivers after each shared eating occasion (eg, meals or snacks); caregivers simply used their phone to click on a study-provided link. Event-contingent assessments included questions on food parenting practices and the child’s food intake during that specific eating occasion. On average, participants took 4.41 (SD 6.35) minutes and a median of 2.77 minutes (IQR 1.90-4.32) to complete each event prompt. The second was signal-contingent assessments, for which caregivers were texted to complete a survey at random intervals situated within 4 time blocks throughout the day (eg, 7 AM-10 AM) to capture momentary variables of interest. Signal-contingent prompts were timed to expire after 1 hour of receipt of the text prompt. On average, participants took 1.74 (SD 2.71) minutes and a median of 1.22 (IQR 0.85-1.82) minutes to complete each signal prompt.

Caregivers were asked to complete 8 days of EMA data collection. A day was considered to be complete if they engaged in 2 event-contingent and 2 signal-contingent assessments; if a parent failed to complete adequate prompts on a specific day, they were given an additional day to complete the required prompts. At baseline, on average, it took parents 9.667 (SD 3.63 days; median 9.0, IQR 8-10) days to achieve 8 complete days. To minimize potential confounding effects of weekly rhythms (eg, weekday vs weekend variations in behavior, mood, or context), all participants began data collection on the same day of the week. This approach, which followed recommendations in the extant EMA literature [47-50], ensures that each participant’s data collection period spanned identical calendar days.

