The distribution of the summary measures (SD, IQR, and entropy) of the longitudinal models described above will be used to derive measures of the consistency and endurance of food parenting practices. A metric of within-day consistency across event characteristics (eg, meal type) will be derived by calculating the distribution of SDs of individual residuals from model (M1) and then calculating an individual’s *z* score relative to this distribution. For example, an individual whose food parenting practices fluctuate substantially across meals will have a large SD of residuals relative to the population, so their *z* score will be relatively large. Consistency *z* scores will be used as predictors of child dietary intake in aim 2. Endurance will be measured by applying a similar *z* score approach but with models that incorporate data across multiple data collection periods. For example, model (M1) will be expanded to include data from times T2 to T4, and endurance *z* scores will be calculated from the distribution of spread summary measures (SD, IQR, and entropy) of the residuals from this expanded model.

Individual food parenting practice domain scores, as well as consistency and endurance metrics, will be used as inputs to a k-means algorithm (implemented using the *kmeans* package in R) to identify clusters of parents observed to use similar food parenting practices over the data collection period. For example, this technique might distinguish subsets of individuals who consistently and primarily use structure and autonomy support practices and those who use these practices less consistently or more commonly use coercive and indulgent practices. We will apply the k-means algorithm with a modest number of clusters (3-5) to ensure that the resulting groups are of sufficient size to accurately characterize them. Descriptive statistics will be used to summarize and compare the food parenting practices as well as demographic and family characteristics of each cluster. Cluster stability metrics and qualitative assessment of the scientific meaningfulness of the clusters will be used to choose a final number of clusters that will define subgroups for inclusion in the following analyses.

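### The consistency z score is an unshrunk SD treated as error-free in the HEI models, and its claimed accuracy rests on a count of 32 that includes prompts carrying no food parenting items

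*Protocol article*

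**What the plan says.** The Overview of the Statistical Analysis Plan fixes the metric. M1 is fitted to domain scores, the SD of each parent's residuals is computed, and that SD is expressed as a z score against the other parents' SDs. These scores "will be used as predictors of child dietary intake in aim 2", and they are also inputs to k-means. The period-specific HEI models enter them next to cluster indicators and covariates. The article mentions no shrinkage, reliability or correction for error in this predictor.

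The Power Analysis, introducing the clustering, says that most parents will have 32 or more observations and concludes that "we anticipate having an adequate sample size to accurately calculate individual summaries of the mean use, consistency, and endurance". Its next paragraphs build the 32 as four responses a day, event or signal, times eight days. Under Ecological Momentary Assessment, the food parenting items belong to the event prompts, and "A day was considered to be complete if they engaged in 2 event-contingent and 2 signal-contingent assessments". The Overview computes domain scores per event prompt and expects two to eight of these a day.

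On power, the article takes an analysis "comparing mean child HEI between 2 groups of size n=100", with a median split on consistency or endurance as its example, and states: "We have 80% power to detect a difference of 0.4 SDs".

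**The concern.** A parent's SD estimated from a limited number of meal reports is partly true variability and partly sampling noise. The z score standardises the sum of the two. Used as a predictor without allowance for the noise, it dilutes a simple association between consistency and HEI and puts some families on the wrong side of a median or quartile split. Hypothesis 4 rests on consistency, so a null result could not be told apart from a noisily measured exposure.

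The article's reassurance on accuracy depends on 32 observations per parent, and that figure includes signal prompts, which carry no domain score.

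**Working it through.** **Inputs from the article.** Two-sided α of 0.05 (Overview); 200 families, hence 100 per group in a median split, 0.4 SD at 80% power, and an HEI SD of 11.6 (Power Analysis); 2 event prompts on a complete day (Ecological Momentary Assessment); 2 to 8 event prompts a day for 8 days (Overview).

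**Input assumed.** The between-parent CV of the true residual SD, τ. The article gives none; the range used is 0.15 to 0.40.

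**1. The plan's own figures.** Power = Φ(d√(n/2) − 1.96).
- n = 100, d = 0.40: 0.40 × √50 = 2.828; Φ(0.868) = 80.7%.
- n = 50, d = 0.57: 0.57 × √25 = 2.85; Φ(0.89) = 81.3%.
- 0.40 × 11.6 = 4.64 HEI units, against a stated value of about 4.7.

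The figures reproduce. No term for error in the grouping variable enters them.

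**2. Number of domain scores per parent per wave.**
- The plan's 32 = (2 event + 2 signal) × 8.
- Event prompts only: 2 × 8 = 16 guaranteed for a parent with eight complete days.
- Expected range: 2 × 8 = 16 to 8 × 8 = 64.

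**3. Sampling error of one SD.** For m independent normal residuals the relative standard error is about 1/√(2(m − 1)). For m = 16 this is 1/√30 = 18.3%. The exact values are 18.4% (m = 16), 12.8% (m = 32) and 8.9% (m = 64).

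**4. Reliability.** With e the relative error from step 3, reliability = τ² / (τ² + (1 + τ²)e²). Example with m = 16 and τ = 0.20: 0.04 / (0.04 + 1.04 × 0.184²) = 0.04 / 0.0752 = 0.53.

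**5. Effect on a median split.** Suppose the difference between families split on their true SD is 0.40 SD. In a simulation (lognormal true SDs, chi-square sampling error, HEI linear in the true SD), families were re-split on the observed SD. The observed difference is close to 0.40 × √reliability, and power follows from the formula in step 1.

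| Event reports | Result | τ = 0.15 | 0.20 | 0.30 | 0.40 |
|---|---|---|---|---|---|
| 16 | Reliability | 0.39 | 0.53 | 0.71 | 0.80 |
| 16 | Observed difference (SD) | 0.25 | 0.29 | 0.34 | 0.36 |
| 16 | Power | 42% | 54% | 67% | 72% |
| 32 | Reliability | 0.58 | 0.70 | 0.84 | 0.90 |
| 32 | Observed difference (SD) | 0.30 | 0.34 | 0.37 | 0.38 |
| 32 | Power | 58% | 66% | 74% | 77% |
| 64 | Reliability | 0.73 | 0.83 | 0.91 | 0.95 |

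In HEI units, a true 4.64 appears as about 2.9 to 4.2 at 16 reports and 3.5 to 4.4 at 32. At 64 reports the approximation in step 5 gives 0.40 × 0.857 = 0.34 SD at τ = 0.15 and 0.40 × 0.972 = 0.39 SD at τ = 0.40, with power of about 68% and 79%.

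Correlation between reports within a day would lower the effective count, as would days without event responses. Neither is in these figures.

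**The case against.** A reader might infer more than the article supports.

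- *That the power statement is wrong.* It is not. A median split can be made only on the observed metric, and for observed groups 0.4 SD at 80% is correct. The lower figures answer another question: the power when 0.4 SD is the difference between the true groups. The article does not say which it means, so this point calls for a clarification.
- *That parents supply at most 32 reports.* The Overview allows up to 64, and parents are asked to report after every shared eating occasion. Sixteen is the floor under minimum compliance. With many reports and wide spread the loss is small.
- *That none of the summaries is accurate.* The evidence concerns the SD. Mean use is better estimated: by Spearman-Brown, its reliability at 16 reports is 0.80 for an assumed intraclass correlation of 0.2. Endurance pools several waves. The accuracy sentence also introduces the clustering, and no effect on the clusters has been quantified here.
- *That the HEI slope must be biased toward zero.* That holds for one predictor with classical error. The planned models combine cluster indicators, z scores and covariates, where the direction is not assured.
- *That rarely endorsed domains are bound to be much worse.* Their sampling error is larger, but differing endorsement rates also widen the true spread between parents, so quoting the noise alone would be one-sided.

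It is also fair that the aims are descriptive, that some modelling detail may sit in a fuller analysis plan, and that the plan defines a subset of regular responders. Against the last point, it adds some sporadic responders back for non-EMA outcomes such as HEI.

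What remains is the method as the article states it: an unshrunk SD used as a predictor with no allowance for its error, defended by a count that is not a count of domain scores.

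**Conclusion.** The point holds for consistency. The guaranteed number of domain scores is 16 per wave for a parent with eight complete days, half the 32 on which the accuracy statement rests, with 16 to 64 expected. One parent's SD then carries a relative error of about 18% at 16 reports, 13% at 32 and 9% at 64. Reliability is about 0.39–0.80, 0.58–0.90 and 0.73–0.95 respectively. If truly more and less consistent families differ by 0.4 SD in HEI, power is about 42–72% at 16 reports and 58–77% at 32.

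These ranges rest on an assumed between-parent CV of 0.15 to 0.40, on independent, roughly normal residuals, and on HEI being linear in the true SD. A simple association is diluted; in the multi-predictor models the bias can go either way. The stated detectable differences stand for observed groups, and the point does not extend to mean use or endurance.

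**What to change.** **Power Analysis text.**
- Replace 32 with the event-only count: 16 guaranteed over eight complete days, 16 to 64 expected.
- Limit the accuracy statement so that it covers consistency only together with a reported reliability.
- Say that the 0.4 and 0.57 SD differences apply to groups formed on the observed metric, and add the attenuation range with its assumptions.

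**HEI models.** Fit M1 as a mixed-effects location-scale model, with a person-specific log residual variance as a second random effect. Carry its uncertainty into the HEI model, either jointly or through posterior draws. An equivalent measurement-error correction would also serve. Report this at least alongside the two-step z score.

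**Cost.** More analysis work, wider intervals for the consistency effect and a less favourable power statement. No new data are needed.
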